## Study design and methods

### Design

The self-help IMI called *CANreduce 3.0* will be evaluated within a three-arm RCT, which will compare a mindfulness-based self-help IMI (arm 1); a CBT-based self-help IMI (arm 2); and a waiting-list control condition (arm 3) in their effectiveness reducing cannabis use among frequent cannabis users. Since the mindfulness-based self-help IMI (arm 1) contains newly-developed contents, testing its effectiveness is of primary interest in the current RCT. The CBT-based self-help IMI (arm 2) is a slightly-adapted version of CANreduce 2.0 [19] and serves as a reference program [52]. Performance of the reference intervention is, thus, not the main consideration; however, if the test (arm 1) and reference intervention (arm 2) both fail to demonstrate a statistically-significant advantage over the control condition, this could suggest that the trial is insensitive, or lacks assay sensitivity. If differences are observed, the difference between the reference intervention (arm 2) and controls can be used to help assess the practical relevance of the difference between arm 1 and the control condition [52].

Consistent with this, a confidence interval approach will be used as an exploratory tool to identify similarities between treatment arms 1 and 2 [53, 54]. The control condition (arm 3) will consist of all the same assessments administered to the other two subject groups (see Section Measures), as well as brief advice on the health risks of cannabis use (e.g., potential short-term and long-term effects). Some screening and brief internet interventions from Swiss addiction counselling also are available on the Internet and, as such, might be accessed by controls, but no links to them will be provided in CANreduce 3.0. Participants who are assigned to the control group will be offered the opportunity to receive the intervention delivered in study arm 1 after they complete the final assessment of the RCT, six months after they register for the study).

The trial has been registered with the ISRCTN registry (date of registration: 09/09/2021) and is traceable as ISRCTN14971662 (http://www.isrctn.com/ISRCTN14971662). It also has been approved by the Ethics Committee of the Faculty of Arts and Social Science at the University of Zurich, Switzerland (approval number: 20.4.17). Any important protocol modifications would be reported to this Ethics Committee.

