### Hypotheses

The following detailed study hypotheses for the main outcome (i.e., reduction in the monthly days of cannabis use between baseline and the 3- and 6-month follow-up assessments) will be tested:A mindfulness-based self-help IMI for the reduction of cannabis use (study arm 1) is more effective than being on a waiting list (control condition, study arm 3).A CBT-based self-help IMI for the reduction of cannabis use (study arm 2) is more effective than being on a waiting list (control condition, study arm 3).A mindfulness-based self-help IMI for the reduction of cannabis use (study arm 1) is at least as effective as a CBT-based self-help IMI (study arm 2).

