### Data analyses

Data will be analyzed according to the ITT principle. Multiple imputation procedures, using the R package *mice* [87], will be used to address missing data. *mice* involves specifying a multivariate distribution for the missing data and drawing imputations from their conditional distributions by Markov chain Monte Carlo (MCMC) techniques. We intend to use 20 imputed data sets, as this has been deemed sufficient [87]. The imputation model will include all primary and secondary outcomes (see above). Adjunct variables, like sociodemographic data, will be included if they improve convergence within the imputation model.

Differences in primary and secondary continuous outcome variables between the two active study arms (1 and 2) at baseline and at both follow-up points will be tested using linear mixed models (LMM). The LMMs will be specified to model clusters and repeated measures by defining random effects for study condition and time (repeated measures). Appropriate distributions for non-normal continuous outcomes will be specified (e.g., negative binomial, zero-inflated). In addition to the ITT analyses, per-protocol analyses will be performed.

To investigate the exploratory research question of whether study arm 1 (mindfulness-based self-help IMI) results in a similar reduction in days of cannabis use as study arm 2 (CBT-based self-help IMI), a confidence interval approach will be used for the ES of the difference between these two study arms, using a two-sided 0.05 level of significance [54]. The equivalence margin is a priori set at d = 0.20, corresponding to the smallest value that would constitute a relevant effect [88]. The upper bound of the 95% CI for the ES will be compared against the predefined equivalence margin of d = 0.20 and must be below the margin to show equivalence.

Additional exploratory regression analyses will be conducted to determine whether baseline variables predict the frequency or quantity of cannabis use, severity of dependence (SDS), reduced psychiatric symptoms (PHQ-9, GAD-7), perceived stress (PSS-10) and mindfulness (MAAS) at 3 and/or 6 months follow-up, treatment retention, and adherence. For these analyses, we will use linear, multinomial, or binary regression models, depending on the scale used for the outcome measure. Treatment retention and client satisfaction will be compared between study arms one and two by Pearson chi-square analysis at week 6 (intervention end).

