### Power analysis

Following best-practice procedures for LMM, power analysis was based on a Monte Carlo simulation. Based on pre-specified LMM model parameters, new values for the primary outcome were simulated and tested by z-tests for the comparison between study arms 1 and 3 (main hypothesis). This procedure was iterated 1000 times using simulated replicates. Power resulted from the number of significant effects identified across simulations (see [89]). The model parameters were derived from the CANreduce 2.0-RCT [19], due to its similar study design and measurements. We estimated a two-level Poisson generalized linear mixed model (GLMM) with random slopes and fixed effects for "measurement time", "study condition", and "condition*time". The CANreduce 2.0 model estimate yielded an effect of b = -0.069 (*p* = 0.07) for the interaction. This value was reduced to -0.06 for the power analyses to account for the smaller ES that have been established in meta-analyses [10]. The simulation indicated a power > 80% for *n* = 210 per study arm. Hence, a total sample of 630 frequent cannabis users will be targeted.

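### The Data analyses section assigns the mixed models to arm 1 versus arm 2 and specifies no contrast with the waiting list, which the trial's first two hypotheses and its sample size rest on

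*Protocol article*

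**What the plan says.** The Hypotheses section lists three hypotheses on the reduction in monthly days of cannabis use from baseline to the 3- and 6-month follow-ups, and says they will be tested. The first two are superiority over the waiting list: "study arm 1) is more effective than being on a waiting list (control condition, study arm 3", and the same for the CBT arm, "study arm 2) is more effective than being on a waiting list (control condition, study arm 3". The third is that arm 1 is at least as effective as arm 2.

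The Design section says of arm 1 that "testing its effectiveness is of primary interest in the current RCT". It uses arm 2 as a reference and says the trial may lack assay sensitivity if the two active arms "both fail to demonstrate a statistically-significant advantage over the control condition".

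The Power analysis section simulated the primary outcome, "tested by z-tests for the comparison between study arms 1 and 3 (main hypothesis"), and arrived at 210 per arm, 630 in total.

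The Data analyses section names the differences that the mixed models will test: "Differences in primary and secondary continuous outcome variables between the two active study arms (1 and 2) at baseline and at both follow-up points". Its other between-arm analyses are a confidence-interval comparison of arms 1 and 2, and chi-square comparisons of retention and satisfaction between arms 1 and 2. The first of these is introduced with "To investigate the exploratory research question of whether study arm 1".

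**The concern.** The analysis section names a contrast, and it is not the one the trial was designed around. The article treats the similarity of the two active programmes as exploratory, yet the only contrast it gives the outcome models is between those two programmes. The contrast that decides whether the new mindfulness programme works is not specified there.

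This matters for three reasons. First, the powered comparison should be the analysed comparison, and the text should show that it was fixed in advance. Second, the assay-sensitivity reading in Design cannot be applied without arm 1 versus arm 3 and arm 2 versus arm 3. Third, the analysis section also leaves the outcome distribution open, with negative binomial and zero-inflated given as examples. Study personnel are not blinded, and data are to be extracted at several time points. With the main contrast unspecified as well, the published text gives little protection against a charge that the deciding analysis was chosen after the data were seen.

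**Working it through.** The point concerns what the sections say, so the check sets them side by side by contrast.

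| Contrast | Hypotheses | Design | Power analysis | Data analyses |
|---|---|---|---|---|
| Arm 1 vs arm 3 | Hypothesis 1, to be tested | Primary interest; needed for assay sensitivity | Main hypothesis; basis of the sample size | Not named |
| Arm 2 vs arm 3 | Hypothesis 2, to be tested | Needed for assay sensitivity and to judge practical relevance | Not covered | Not named |
| Arm 1 vs arm 2 | Hypothesis 3 (at least as effective) | Exploratory, by confidence interval | Not covered | Mixed models, confidence interval, chi-square |

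**Step 1: is arm 3 mentioned in Data analyses?** No. The imputation paragraph names no arms. The mixed-model sentence, the confidence-interval paragraph and the chi-square sentence each name arms 1 and 2. The exploratory predictor regressions name no between-arm contrast.

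**Step 2: is a test against the waiting list described elsewhere?**
- For arm 1 versus arm 3, partly. Power analysis describes a two-level Poisson mixed model with time, condition and their interaction, and z-tests of arm 1 against arm 3. That describes the simulation, whose parameters were derived from the earlier CANreduce 2.0 trial. It shows the intention but does not commit this trial's analysis to that model.
- For arm 2 versus arm 3, no. Hypotheses and Design require the comparison, but no method is given for it in any section.

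**Step 3: count.** Hypotheses with a named contrast in Data analyses: 1 of 3. Hypotheses without one: 2 of 3, including the only one the sample size was calculated for.

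**Step 4: the plan's own figures.** 3 × 210 = 630 agrees with the stated total. The stated power above 80% cannot be reproduced, because the baseline mean, random-effect variances, time coding and dropout used in the simulation are not given. The point does not depend on that figure; it depends only on which contrast the figure refers to, which is arm 1 versus arm 3.

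**The case against.** The strongest reply is that the intention is plain. Hypotheses commits to testing all three hypotheses. The abstract says the analysis will mainly use (generalized) linear mixed models and describes both interventions as compared with the waiting list. Power analysis practically writes out the arm 1 versus arm 3 test. On this view the sentence in Data analyses is a drafting slip, and a statistical analysis plan that is not shown may already have it right.

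Much of that stands, and it rules out several stronger readings:

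- A reader might infer that the trial has no plan to test its main question. The documents do not support this. Two sections need reconciling, and the arm 1 versus arm 3 test can be inferred.
- A reader might infer that the 210 controls are left out of the model. The sentence says which differences are tested, not whose data are fitted. The next sentence refers to study condition without limiting it to two levels, so a three-arm fit is compatible with the wording.
- A reader might take the arm 1 versus arm 2 mixed model to be the trial's confirmatory analysis. The article never labels it so.
- A reader might see the confidence-interval paragraph as the same analysis repeated. It asks a different question: similarity in days of use against a margin of d = 0.20, rather than differences across primary and secondary outcomes.

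The appeal to an unseen analysis plan does not dispose of the point. Condensing a protocol explains missing detail, but here a contrast is stated and it is the wrong one for the main hypothesis. An analysis plan that tested arm 1 against arm 3 would depart from the published sentence, and one that followed the sentence alone would not test the main hypothesis. For arm 2 versus arm 3 there is nothing elsewhere in the article to infer a test from.

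**Conclusion.** The contradiction is real and should be corrected before analysis. Data analyses names arm 1 versus arm 2 as the contrast for the mixed models and specifies none with the waiting list, while Hypotheses, Design and Power analysis all require contrasts with it. Two of three hypotheses are affected, one of them the main hypothesis. For arm 1 versus arm 3 the gap is one of specification, since the intended test can be inferred from the power simulation. For arm 2 versus arm 3 no test is described at all.

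The conclusion rests on the article's text alone and needs no numerical assumption. A drafting slip is the likely cause, but the slip sits in the sentence that specifies the outcome models for the primary endpoint.

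**What to change.** Rewrite the mixed-model sentence in Data analyses so that:

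- the (generalized) linear mixed model covers all three randomised arms, with condition, time and condition-by-time;
- arm 1 versus arm 3 is the primary contrast and arm 2 versus arm 3 the second, at the 3- and 6-month follow-ups named in Hypotheses;
- arm 1 versus arm 2 is exploratory, alongside the existing confidence-interval analysis;
- the same contrasts apply to secondary outcomes collected in all arms, while the satisfaction questionnaire (CSQ-I), which Table 3 restricts to arms 1 and 2, stays a two-arm comparison.

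A single three-arm model is not the only acceptable form; pairwise models that deliver the same contrasts would also remove the contradiction. Any separate statistical analysis plan should carry the same wording. The cost is a change of text, with no new data, no additional participants, and no change to the sample size from the wording alone.

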#### Assessments, compensation, and randomization

Once they complete a baseline questionnaire (t0), participants will be randomly allocated by a random number generated by the server to one of three study arms. The masking technique will be partially single-blinded: participants will know if they were assigned to the waiting list control group or to one of the two intervention groups. However, in the latter case, they will be unaware of the particular intervention that they are receiving. The risk of disappointing participants who fail to receive their preferred intervention is essentially eliminated by describing both interventions as ‘an optimized version of a previous program’ without providing further details. Those participants who are assigned to study arms 1 or 2 can then immediately commence with the program, whereas controls assigned to study arm 3 will be informed that they must wait for six months to access the intervention. Besides the baseline questionnaire (t0), participants in all study arms will be asked to fill out an online assessment at six weeks (i.e., for study arms 1 and 2: immediately after they conclude the program; t1), three months (t2) and 6 months (t3) after their baseline assessment. Participants will earn 20 Swiss Francs for completing the 3-month follow-up assessment (t2) and 30 Swiss Francs for completing the 6-month follow-up assessment (t3). They can individually decide whether they wish to receive the total amount as an online voucher or to donate it to a charity. The study personnel is not blinded.

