
**Table 3 Tab3:** Overview of all measures and their measurement time points

	**Assessment instruments**	**Base-line (t**_**0**_**)**	**6 weeks (t**_**1**_**)**	**3 months follow-up (t**_**2**_**)**	**6 months follow-up (t**_**3**_**)**
1	Socio-demographics (age, gender, sexual orientation, educational attainment, migration background, financial situation)	X			
2	Cannabis Use Disorders Identification Test (CUDIT-R)	X	X	X	X
3	*Cannabis use*				
3a	Consumption Patterns (Years of Use, 30-day point prevalence of cannabis and CBD abstinence, Type of Consumption)	X	X	X	X
3b	Defining the personal standard joint	X			
3c	TLFB (Cannabis use frequency and amount for the last 7 days in standard joint units)	X	X	X	X
4	Severity of Dependence Scale (SDS)	X	X	X	X
5	Short version of the Alcohol Use Disorders Identification Test (AUDIT-C)	X		X	X
6	National Institute on Drug Abuse *Screening (NIDA ASSIST)*	X		X	X
7	Drug Abuse Screening Test (DAST-10)	X			
8	Perceived Stress Scale (PSS-10)	X	X	X	X
9	Patient Health Questionnaire for Depression (PHQ-9)	X		X	X
10	Generalized Anxiety Disorder Screener (GAD-7)	X		X	X
11	Adult ADHD Self-Report Scale (ASRS-V1.1)	X			
12	Mindfulness Attention Awareness Scale (MAAS)	X	X	X	X
13	Comprehensive Inventory of Mindfulness Experiences (CHIME)	X			
14	Previous experience in meditation (no official instrument)	X			
15	Client Satisfaction Questionnaire for Internet Interventions (CSQ-I)		X^a^		
16	Negative effects, according to Rozental et al. (2015)		X		
17	Use of any services besides CANreduce			X	X
18	Adherence and Retention^b^		X		

^a^ Only for study arms 1 and 2

^b^ Adherence and retention are constructs measured indirectly and not part of a questionnaire

The primary study outcome is the number of days of cannabis use over the preceding 30 days.

Secondary outcomes are quantity and frequency of cannabis use over the last seven days’; scores for the SDS, AUDIT-C, NIDA-ASSIST, PSS-10, PHQ-9, GAD-7, MAAS, and CSQ-I., and any negative effects attributed to the program.

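### The analysis section tests arm differences at baseline and at each follow-up, the hypotheses and power model concern change, and no stated contrast makes efficient use of the baseline value

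*Protocol article*

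**What the plan says.** All references are to the protocol article.

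- **Hypotheses.** The main outcome is described as "reduction in the monthly days of cannabis use between baseline and the 3- and 6-month follow-up assessments". Three arm comparisons are listed: 1 versus 3, 2 versus 3, and 1 versus 2.
- **Measures.** "The primary study outcome is the number of days of cannabis use over the preceding 30 days".
- **Data analyses.** Arm differences "at baseline and at both follow-up points will be tested using linear mixed models (LMM". The object of the test is "Differences in primary and secondary continuous outcome variables between the two active study arms (1 and 2) at baseline and at both follow-up points". The sentence names only arms 1 and 2. The model is described by "defining random effects for study condition and time (repeated measures". No fixed-effect terms, baseline covariate or constraint on baseline means are named there. Missing data are handled by multiple imputation with 20 data sets. The arm 1 versus arm 2 effect size gets a 95% confidence interval whose upper bound is compared with d = 0.20; this comparison is labelled exploratory.
- **Power analysis.** "We estimated a two-level Poisson generalized linear mixed model (GLMM) with random slopes and fixed effects for" time, condition and their interaction. The interaction is the effect that is powered, for arm 1 versus arm 3.
- **Assessments, compensation, and randomization.** "Once they complete a baseline questionnaire (t0), participants will be randomly allocated".

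**The concern.** The sections describe different contrasts. The hypotheses and the power model concern change over time. The sentence that names the test concerns differences at each time point, including baseline. A reader could not tell from the article which coefficient will be reported as the result.

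Two consequences follow. First, a significance test between randomised arms on a variable measured before allocation has a null that is true by design. A significant result there carries no information about the programmes and invites post hoc adjustment. Second, whether the reported contrast turns out to be the follow-up level or the change, the baseline value of the same outcome, which is collected from every participant before allocation, is not used as well as it could be. Precision is at a premium here: the Discussion expects relatively large drop-out, and the unadjusted interval for arm 1 versus arm 2 is almost as wide on each side as the margin it is compared with.

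**Working it through.** **The plan's own figure.** The article states more than 80% power at 210 per arm for an interaction of b = -0.06. By normal approximation, 80% two-sided power needs SE(b) ≤ 0.06/(1.960 + 0.842) = 0.0214. The earlier estimate, b = -0.069 with p = 0.07, implies SE = 0.069/1.812 = 0.0381 if p is two-sided. If the SE scales with 1/√n, 210 per arm reaches 80% only if the earlier model had about 210 × (0.0214/0.0381)² ≈ 66 or fewer per arm. The article does not give that number, so the stated power can be neither confirmed nor refuted. It does confirm that the powered quantity is a difference in change.

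**Baseline test.** Allocation comes after the baseline questionnaire, so the arm means differ only by chance. In simulation at 210 per arm (4,000 runs for each r), the baseline test rejected in 4.9% to 5.2% of runs, which is the nominal rate.

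**What the follow-up contrast estimates.** After multiple imputation each analysed data set is complete. In a linear mixed model with baseline among the outcomes, categorical time and free arm-by-time means, the arm contrast at a follow-up equals the raw difference in follow-up means, and the condition-by-time contrast equals the difference in mean change. This is exact for linear models with complete data and approximate for count models.

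**Variances.** With equal SDs and correlation r, relative to the follow-up level:

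- level: 1
- change: 2(1 − r)
- baseline-adjusted: 1 − r²

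Since 2(1 − r) − (1 − r²) = (1 − r)², adjustment is more precise than change for every r < 1. It is more precise than level for every r other than 0.

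**Power.** Inputs: n = 210 per arm (Power analysis); two-sided 0.05 (stated only for the arm 1 versus arm 2 interval, assumed here for the tests); r assumed. Fix the effect so that the adjusted test has noncentrality 2.80, that is 80% power. The level test then has noncentrality 2.80√(1 − r²) and the change test 2.80√((1 + r)/2). Power is Φ(noncentrality − 1.96).

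| r | Level | Change | Adjusted |
|---|---|---|---|
| 0.4 | 73% | 65% | 80% |
| 0.5 | 68% | 68% | 80% |
| 0.6 | 61% | 71% | 80% |
| 0.7 | 52% | 73% | 80% |

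Level beats change below r = 0.5 and loses to it above.

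**Arm 1 versus arm 2.** In SD units the level SE is √(2/210) = 0.0976. At r = 0.6 the half-widths (1.96 × SE) are:

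- level: 1.96 × 0.0976 = 0.191
- change: 0.191 × √0.8 = 0.171
- adjusted: 0.191 × √0.64 = 0.153

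With a true difference of zero, the chance that the upper bound is below 0.20 is Φ((0.20 − half-width)/SE): 54%, 63% and 73% respectively.

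**Chance imbalance.** The baseline difference between two arms has SD 0.098 in SD units. A 0.10 SD imbalance moves a level contrast by 0.10r and a change contrast by −0.10(1 − r). At r = 0.6 these are +0.06 and −0.04. Baseline adjustment removes it.

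**The case against.** The strongest reply is that most of this is inferred. The sentence at issue concerns arms 1 and 2 only. For the main hypothesis, arm 1 versus arm 3, the only model described is in the Power analysis section, and it contains the interaction. The article nowhere says that follow-up comparisons are unadjusted, and covariates and exact contrasts are commonly left to a SAP that is not shown. All of that is correct, and it limits the point. It does not remove it: the article names a test at baseline and at each follow-up, which is not what its hypotheses and power sections describe, and even the interaction model is not baseline-adjusted when baseline means are left free.

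Several stronger readings are tempting but not supported:

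- **That the plan tests the wrong hypothesis.** On a linear scale under randomisation, equal follow-up levels and equal reductions are the same null. Level, change and adjusted contrasts estimate the same effect with different precision.
- **That the main comparison loses 28 points of power.** That figure (80% to 52% at r = 0.7) belongs to a pure level test. Against the change contrast suggested by the power model, the loss is 7 to 15 points.
- **That false positives are inflated.** A level test's error rate is about 14% to 33% only within the 5% of trials whose baseline difference happens to be significant. Over all trials it is 5%.
- **That spurious baseline findings have a 37% chance.** 1 − 0.95⁹ = 0.37 assumes nine independent outcomes; several overlap, so it should not be relied on.

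It is also fair that the count models, drop-out and imputation mean these percentages do not transfer exactly.

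**Conclusion.** The point holds as one of coherence and efficiency and should be acted on. The sections disagree on the contrast, and the baseline test is uninformative whatever r is. Leaving baseline means free costs 7 to 15 points of power for a change contrast and 7 to 28 for a level contrast, over r = 0.4 to 0.7. For the arm 1 versus arm 2 interval at r = 0.6, adjustment raises the chance of an upper bound below the margin by 10 points over change or 19 over level, if the arms are truly equal.

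These sizes rest on 210 per arm, complete normal data, equal SDs and assumed values of r; the direction of the gain does not depend on the particular r. Chance imbalance entering the result is not systematic bias.

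**What to change.** In Data analyses:

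1. Delete the test at baseline and report baseline by arm descriptively.
2. State that the arm contrasts at 3 and 6 months (1 versus 3, 2 versus 3 and 1 versus 2) come from a linear or generalised linear mixed model with fixed condition, time and condition-by-time terms. Either include the baseline value of the same outcome as a covariate, or keep baseline among the outcomes and constrain its mean to be equal across arms.
3. Take the arm 1 versus arm 2 effect size and its 95% interval from that same model.

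This also gives the main hypothesis a named test in the analysis section and aligns that section with Hypotheses and Power analysis. The cost is about two sentences and one change to the model formula. No new data or participants are needed, because baseline is collected from everyone before allocation.

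### The analysis section makes study condition a random effect and names no fixed arm or arm-by-time effect, which contradicts the fixed-effects model used for power

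*Protocol article*

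**What the plan says.** The Data analyses section says that differences in continuous outcomes "between the two active study arms (1 and 2) at baseline and at both follow-up points will be tested using linear mixed models (LMM"). On structure it then says: "The LMMs will be specified to model clusters and repeated measures by defining random effects for study condition and time (repeated measures"). It lists no fixed effects, and it does not say at which level the random effects sit.

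The Power analysis section describes a "two-level Poisson generalized linear mixed model (GLMM) with random slopes and fixed effects for" measurement time, study condition and the product of the two. Simulated outcomes were "tested by z-tests for the comparison between study arms 1 and 3 (main hypothesis"). The effect carried into the simulation is the interaction. The previous trial "yielded an effect of b = -0.069 (*p* = 0.07) for the interaction", and "This value was reduced to -0.06 for the power analyses". The result is power above 80% at 210 per arm, 630 in all.

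On allocation, the section on assessments, compensation and randomization says that "participants will be randomly allocated by a random number generated by the server to one of three study arms". The Hypotheses section sets out three specific comparisons: arm 1 with arm 3, arm 2 with arm 3, and arm 1 with arm 2.

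**The concern.** A factor is treated as random when its levels stand for a larger population and the interest lies in their variance. Study condition is the opposite case. It has three levels (two if the model covers only the arms that the analysis sentence names), they were chosen by design, and the hypotheses are about the differences between them. Such a factor belongs in the fixed part of the model.

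Two things are at stake. If the sentence is followed as written, the model does not return the quantity that the hypotheses need, and what it does return for each arm is pulled towards the overall mean. Also, the two sections describe different models, so a reader cannot tell whether the power statement applies to the analysis that will be run. This goes beyond detail that an article leaves to the analysis plan: the article chose to state the random structure, and what it states conflicts with its own power section.

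**Working it through.** **1. The plan's own figure.** The power above 80% cannot be reproduced, because the variance components, the time coding and the previous trial's sample size are not given.

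- Standard error needed for 80% power at b = −0.06, assuming a two-sided 0.05 test (the plan gives no level for this z-test): 0.06 / (1.960 + 0.842) = 0.0214. A one-sided test would need 0.0241.
- Standard error implied by the previous trial (b = −0.069, p = 0.07, so |z| ≈ 1.81): 0.069 / 1.81 ≈ 0.038.
- Information needed relative to that trial: (0.0381 / 0.0214)² ≈ 3.2, or about 2.5 if one-sided.

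An illustrative Poisson simulation used 210 per arm and a robust marginal test. It assumed a baseline mean of 22 days, a random-intercept SD of 0.3, and time coded 0–2 or 0–3. Without dropout, power was 86–99% at a slope SD of 0.1, 67–69% at 0.2 and 21–24% at 0.4. With 50% dropout and a slope SD of 0.1 it was 51–84%. These inputs are assumptions, so the plan's figure is neither confirmed nor refuted.

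**2. The two models side by side.**

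| | Data analyses | Power analysis |
|---|---|---|
| Condition | random | fixed |
| Time | random | fixed, plus random slopes |
| Condition by time | not mentioned | fixed; the powered effect |
| Test | not tied to a coefficient | z-test, arm 1 versus arm 3 |

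The coefficient that was powered does not appear in the model as the analysis section describes it.

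**3. What a literal random condition effect does to an arm difference.** Take two arms of n participants, residual variance s², observed difference D, and z² = D² / (2s²/n).

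- Between-arm mean square: nD²/2 = s²z².
- REML variance of condition: (s²z² − s²)/n = (s²/n)(z² − 1), set to zero if negative.
- Fraction of D kept in the predicted difference: (z² − 1)/z² = 1 − 1/z².

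| z | kept | lost (1/z²) |
|---|---|---|
| 2.8 | 87% | 13% |
| 1.96 | 74% | 26% |
| 1.5 | 56% | 44% |
| 1 or less | 0% | 100% |

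With three arms the factor is 1 − 1/F, where F is the three-arm F statistic.

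**4. Average effect at the planned size.** This is an illustrative one-way model in SD units with 210 per arm. A fixed contrast has 80% power at d = 2.80 × √(2/210) = 0.273. In 200,000 simulated trials the fixed contrast averaged 0.273. With condition random, the predicted arm 1 versus arm 3 difference averaged 0.235 with two arms (86%) and 0.21–0.22 with three (76–81%, depending on where the third arm lies). A check with 150 actual REML fits gave 0.214 against 0.271 (79%), with many boundary or convergence warnings. With no true difference, the condition variance is estimated as exactly zero in 68% of two-arm trials (the chance that χ² on 1 df is below 1) and in 63% of three-arm trials (1 − e⁻¹).

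Steps 3 and 4 concern a main effect. No shrinkage was computed for the condition-by-time effect.

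**The case against.** The strongest reply is that the intended model can be recovered from the article itself. The Power analysis section gives fixed condition, time and interaction in a two-level model. The Data analyses section says that arm differences will be tested and that a 95% confidence interval will be formed for arm 1 versus arm 2. Both need a fixed contrast. The analysis sentence lists no fixed effects at all, so it never says that condition is not fixed. This is a fair argument, and loose drafting is quite possible. It does not remove the contradiction: the one sentence that describes the analysis model puts condition in the random part, and nothing in that section corrects it.

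Some further points stand on the other side.

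- The word clusters can fairly mean participants with repeated measures inside them, so it is not an error in itself.
- A random condition coefficient at participant level, uncorrelated with the intercept, can be estimated. It allows between-participant variance to differ by arm. With condition also fixed, it leaves a valid contrast. That fixed effect is what the text does not state.
- A reader might infer that no valid test of any kind would exist. That is too strong. A global F test of heterogeneity between arms remains available, although it gives no directional arm 1 versus arm 3 effect and does not address the powered interaction.
- The 1/z² figures hold only for a two-arm main-effect model with condition random and not fixed. They show what one literal reading would do and do not forecast the trial's result.

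**Conclusion.** The Data analyses section specifies study condition as random, states no fixed condition or condition-by-time effect, and so contradicts the Power analysis section. Read literally, it gives no coefficient for the comparisons in the Hypotheses section, and it shrinks arm differences. In the simple two-arm model the loss is 13% at z = 2.8, 26% at z = 1.96, 44% at z = 1.5, and everything at z of 1 or less. The stated power then refers to a different model from the one described for analysis.

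Two stronger conclusions do not follow. A reader might infer that the hypotheses will go untested, but that assumes the literal reading, and the wording may be no more than imprecise. A reader might also infer that 630 participants is the wrong number. The documents do not give the inputs to judge that, and the mismatch between models says nothing about it. That the analysis sentence names only arms 1 and 2 is a separate matter.

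**What to change.** Replace the sentence on random effects. State fixed effects for study condition, time and condition by time. State participant-level random effects: a random intercept and, if it converges, a random slope for time. Code time as in the power model. Delete the reference to random effects for study condition. The word clusters may stay if it is said to mean participants.

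This costs one sentence and leaves the design, the sample size and the data collection unchanged. It brings the analysis into line with the power statement without a new simulation. If categorical time is preferred, there is no longer a single interaction coefficient of −0.06 per arm comparison, and the power statement must be re-simulated for the contrast chosen.
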